### Randomization

The study will obtain informed consent at the baseline clinic visit at 8^+ 0^ to 13^+ 6^ weeks’ gestation. Only those women who meet the inclusion criteria, consent and complete the baseline assessment will be randomly assigned to either intervention or control group.

The 100 participants from each hospital will be randomly allocated at a 1:1 ratio to either the intervention group or the control group by the study staff, stratified by the categorical variables of age (< 30 and ≥ 30 years), pre-pregnancy BMI (< 28 and ≥ 28 kg/m^2^), and history of delivery with randomly determined block sizes of 4. Neither the staff nor the participants will be blinded to the group assignment due to the nature of the intervention program. The process of the randomization will be supervised by another study staff and recorded in a Microsoft EXCEL database.

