#### Sociodemographic characteristics and outcomes 

Participants’ sociodemographic characteristics including age, educational level, occupation, socio-economic status (health insurance, household income last year), smoking and alcohol consumption, medical and reproductive history will be assessed at the baseline survey at 8 to 13^+ 6^ weeks’ gestation. Other outcomes including sleep quality, quality of life, and mental health, et al.

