### Outcomes

*The primary outcomes* of this study are the total GWG up to 32^+ 0^−35^+ 6^ weeks’ gestation and the GWG prior to the OGTT screening at 24^+ 0^−27^+ 6^ weeks’ gestation. Both will be calculated by subtracting the pre-pregnancy weight from the weight measured at the respective time points.

*The secondary outcomes *include rate of GWG per week. Weekly rate of GWG will be defined as GWG divided by the number of weeks between the date of LMP and the midterm survey (24^+ 0^ to 27^+ 6^ weeks’ gestation) and the terminal survey (32^+ 0^ to 35^+ 6^ weeks’ gestation). Weekly rate of GWG between study clinical visits at 8^+ 0^ weeks’ and 27^+ 6^ weeks’ gestation, and at 8^+ 0^ and 35^+ 6^ weeks’ gestation will be calculated by dividing the amount of weight gain between visits by the weeks of gestation between visits. The proportion of women who exceed the 2009 IOM guidelines’ weekly rate of GWG will also be assessed, and it was defined as being above the upper limit of the first trimester (2.0 kg) plus the upper limit of the weekly rate (0.33 kg/week for overweight with BMI ranging from 24.0 to 28.0 kg/m^2^, 0.27 kg/week for obesity with BMI ≥ 28 kg/m^2^), times the number of weeks in the second and third trimesters.

Other secondary outcomes include incidence of GDM diagnosed according to IADPSG criteria (FPG ≥ 5.1 mmol/L, and/or 1-h blood glucose ≥ 10.0 mmol/L, and/or 2-h blood glucose ≥ 8.5 mmol/L), rate of preeclampsia/gestational hypertension (preeclampsia was defined according to the criteria of the ACOG, i.e. systolic blood pressure of ≥ 140 mmHg or diastolic blood pressure of ≥ 90 mmHg occurring after 20 weeks of gestation in a previously normotensive woman combined with new-onset proteinuria of ≥ 0.3 g/24 h. Gestational hypertension was defined similarly but without the presence of proteinuria.), incidence of cesarean delivery, absolute/mean infant birth weight, incidence of macrosomia (with infant birth weight ≥ 4000 g), and absolute/mean Apgar scores at 1–5 min (Apgar scores at 1–5 min evaluate the baby’s heart rate, respiratory effort, muscle tone, reflex irritability, and color. Each category is scored from 0 to 2, and the total score ranges from 0 to 10. A higher Apgar score indicates that the newborn is in good health.).

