### Statistical analyses

Baseline characteristics of participants will be reported by using descriptive statistics. Statistical analyses will be based on the intention-to-treat principle, and include all women recruited with BMI ≥ 24 kg/m^2^. Multiple linear regression models/Generalized linear mixed models will be used to examine the primary and secondary outcomes at 24^+ 0^−27^+ 6^ and 32^+ 0^−35^+ 6^ gestational weeks, at delivery, at 42 d, 6 m, and 12 m after delivery, and the models will be adjusted for the clustering effect and the baseline outcome values. Chi-squared tests will be used to compare conditions on the proportion of women who exceed the 2009 IOM guidelines’ weekly rate of GWG, and other dichotomous outcomes. We will also analyze whether the outcome disparities between the intervention and control groups vary by hospitals, BMI status before pregnancy, etc. All results will be considered statistically significant as two-side *P* < 0.05. Statistical analyses will be conducted by using R software 4.4.1.

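### The stated analyses of cesarean delivery leave out previous cesarean, a baseline predictor obtainable from data already collected, and so give up precision

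*Protocol article*

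**What the plan says.** Under Outcomes, the other secondary outcomes include "incidence of cesarean delivery, absolute/mean infant birth weight, incidence of macrosomia". Nothing there restricts cesarean to a subset of women or splits it by earlier mode of delivery.

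Statistical analyses makes two statements that could apply to it:
- "Chi-squared tests will be used to compare conditions on the proportion of women who exceed the 2009 IOM guidelines" weekly rate, "and other dichotomous outcomes". Cesarean yes/no is a dichotomous outcome, so this covers it. No stratum or covariate is named.
- "Generalized linear mixed models will be used to examine the primary and secondary outcomes", at time points that include delivery, and "the models will be adjusted for the clustering effect and the baseline outcome values".

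The analysis set is intention-to-treat. Effect variation is to be examined by hospital, pre-pregnancy BMI status and further unnamed factors.

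Randomization stratifies by age, BMI "and history of delivery with randomly determined block sizes of 4". The levels of the delivery-history factor are not defined. Under Sociodemographic characteristics and outcomes, "medical and reproductive history will be assessed at the baseline survey". The eligibility criteria exclude neither parous women nor women with an earlier cesarean; the surgical exclusion covers only bariatric surgery and recent operations on important organs.

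**The concern.** A previous cesarean is likely to be a strong predictor of cesarean in the current pregnancy, and it is known before randomisation. If so, it accounts for much of the spread in this outcome, and an analysis that ignores it carries variance that could have been removed.

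The mixed models do not fill the gap. Cesarean in this pregnancy has no baseline value, so adjusting for baseline outcome values adds nothing here. Clustering is a different matter.

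The randomisation factor may not fill it either. If delivery history means parous or not, it puts women with only vaginal births in the same stratum as women with a previous cesarean. In any case, the analysis section does not name it as a covariate.

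Improving delivery outcomes is part of the stated aim of the trial. What is at stake is how precisely one secondary outcome is estimated, and whether adjustment for delivery history is fixed in advance or chosen after results are known in an unblinded trial.

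**Working it through.** **Plan's own figure.** The article gives no power or rate for cesarean. Its only power statement (80%) concerns weight gain and is not used here.

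**Inputs from the article.** 200 women, 1:1 allocation, 10% attrition: 100 × 0.9 = 90 per arm. Two-sided 5% level.

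**Inputs assumed.** Share with a previous cesarean f = 5–30%. Repeat-cesarean rate r = 95% in both arms (80% as a check). Cesarean in women without a previous cesarean: 35% control, 20% intervention.

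**Crude comparison.** The arm rates are pC = f·r + (1−f)·0.35 and pT = f·r + (1−f)·0.20, so the difference is (1−f) × 15 points. Power = Φ[(d − 1.96·SE0)/SE1], with SE0 from the pooled rate and SE1 from the separate rates.

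At f = 20%, r = 95%:
- pC = 0.19 + 0.28 = 0.47; pT = 0.19 + 0.16 = 0.35; d = 0.12
- SE0 = √(2 × 0.41 × 0.59/90) = 0.0733
- SE1 = √[(0.47 × 0.53 + 0.35 × 0.65)/90] = 0.0728
- power = Φ[(0.12 − 0.1437)/0.0728] = 37%

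**Stratified by previous cesarean (yes/no).** The expected difference is the same, but the variance is taken within strata: (2/90)[f·r(1−r) + (1−f)·0.275 × 0.725]. At f = 20% this is (2/90)(0.0095 + 0.1595) = 0.00376, SE 0.0613, and power = Φ(0.12/0.0613 − 1.96) = 50%.

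**Women without a previous cesarean only.** At f = 20% there are 72 per arm, the difference is 15 points, SE0 = 0.0744, SE1 = 0.0734, and power = 52%.

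| Share f | Repeat r | Overall difference | Crude | Stratified | No previous cesarean only |
|---|---|---|---|---|---|
| 5% | 95% | 14.25 points | 54% | 59% | 59% |
| 10% | 95% | 13.5 | 48% | 56% | 57% |
| 20% | 95% | 12.0 | 37% | 50% | 52% |
| 30% | 95% | 10.5 | 29% | 43% | 47% |
| 20% | 80% | 12.0 | 38% | 45% | 52% |

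A simulation of 40,000 trials per setting agrees: at 10/20/30% and r = 95%, crude power is 49/37/28% and stratified power 57/50/43%. With no effect, the crude test rejects in 4.4–5.0% of trials, so its error rate is kept.

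**Does stratifying remove dilution?** No. At f = 20% the stratum differences are 0 and 15 points, and 0.2 × 0 + 0.8 × 15 = 12, the crude value. The crude risk ratio is 0.35/0.47 = 0.74, and with balanced strata the Mantel-Haenszel ratio is also 0.74. Only the analysis in women without a previous cesarean shows 0.20/0.35 = 0.57.

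**Would parity do as well?** Take an illustrative mix: 20% previous cesarean (90% deliver by cesarean), 25% previous vaginal only (12%), 55% nulliparous (40%).
- Overall rate: 0.18 + 0.03 + 0.22 = 0.43; total variance 0.43 × 0.57 = 0.245.
- Three levels: 0.20 × 0.47² + 0.25 × 0.31² + 0.55 × 0.03² = 0.0687, or 28% of the variance.
- Parity: the parous rate is 0.21/0.45 = 0.467, so 0.45 × 0.037² + 0.55 × 0.03² = 0.0011, or 0.4%.

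Across assumed mixes (previous cesarean 10–25% of women), the three-level factor explains about 15–38% of the variance and parity about 0–3%.

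**The case against.** The strongest reply is that nothing here is wrong. Under randomisation the crude comparison is valid, and its risk difference and ratio are unbiased for all women, the population that the intention-to-treat analysis targets. All of that stands. A reader might infer that the overall effect is biased towards no effect. The documents do not support that: the effect in women without a previous cesarean is a different quantity, not the true value of the same one. Nor is chance imbalance in previous cesarean (SD about 6 points at a 20% share, about 5.2 if strata are parity and half the women are parous) a further harm. It is already in the standard error.

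A reader might also conclude that the randomisation factor cannot represent previous cesarean. The article does not define its levels, so this is unproven. Even as parity, the factor sets apart nulliparous women, who cannot have had a cesarean. Likewise, chi-squared is not the only method named; the mixed models could be meant for cesarean. They still do not use previous cesarean.

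The premise that an earlier cesarean strongly predicts the next mode of delivery is clinical knowledge, not a figure in the article, and the loss is small if few women are affected. Cesarean is one of many secondary outcomes without a power claim, and stratification still leaves power at 43–59% in the scenarios with 95% repeat cesarean. Finally, covariates for secondary outcomes are often left to an analysis plan, which is not shown. That excuses silence, but here the article states a specific unadjusted test.

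**Conclusion.** The concern holds as one of precision, not validity. Neither stated method uses previous cesarean, although the information is to be collected before randomisation. Under the assumptions above, the plain test gives up about 4 to 5 power points if 5% of women have a previous cesarean, about 8 at 10%, 13 at 20% and 14 at 30%. With 80% repeat cesarean and a 20% share, the loss is about 7 points. If delivery history means parity, it does not separate previous cesarean from previous vaginal birth and would recover little of this loss. The direction depends only on previous cesarean being predictive; the size depends on rates that the article does not give. The dilution of the all-women effect is real in these scenarios, but it is a property of the population studied, and stratification does not change it.

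**What to change.** In Statistical analyses, replace the plain chi-squared test for cesarean with a pre-specified risk difference and risk ratio, stratified by or adjusted for a three-level baseline factor: nulliparous, previous vaginal births only, previous cesarean. Mantel-Haenszel estimates would serve, as would a binomial model reported on the risk scale. An adjusted odds ratio alone would not estimate the same all-women effect. State that this estimates the same effect as before, with better precision.

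Add a supporting analysis of cesarean in women without a previous cesarean, labelled as such. It is the only part that addresses dilution. In Randomization, define the levels of the delivery-history factor.

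The cost is a sentence or two. The factor comes from the reproductive history already planned for baseline, and no woman is excluded from the main comparison. The downsides are a slightly more complex analysis and a smaller supporting subgroup (for example 72 rather than 90 per arm at a 20% share).

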### Eligibility and recruitment

The HGWG-pro study will recruit 200 overweight or obese pregnant women from 2 hospitals, with 100 participants from each hospital. Overweight or obesity were determined based on BMI recommendations of the Group of China Obesity Task Force of the Chinese Ministry of Health (overweight: 24 ≤ BMI < 28 kg/m^2^; obese: BMI ≥ 28 kg/m^2^) [22]. Pregnant women receiving usual antenatal care at the two hospitals will be firstly identified through gestational weeks. Only those at 8–14 weeks’ gestation will be further evaluated according to the inclusion criteria: aged between 18 and 40 years, pre-pregnancy BMI between 24 and 40 kg/m^2^ based on weight self-reported and recorded in the electronic medical record (EMR), singleton pregnancy, skilled at using smartphones and WeChat (mobile application), planning to attend regular antenatal care and delivery at Weifang Maternal and Child Health Hospital of Shandong or Tongzhou Maternal and Child Health hospital of Beijing, no contraindications to physical activity according to Physical Activity Readiness Questionnaire (PAR-Q), willing to be randomized and cooperate with regular follow-up visits and sign informed consent.

Exclusion Criteria including women with pre-pregnancy hypertension, severe cardiovascular or cerebrovascular diseases, respiratory disease, hepatic or renal disease, malignant tumors, systemic lupus erythematosus, thyroid disease, severe anemia, and other chronic diseases, cervical insufficiency, multiple pregnancy, continuous vaginal bleeding, diabetes before pregnancy, special dietary needs (e.g. vegetarianism), severe psychiatric disorders, with a history of bariatric surgery or other surgical history involving important organs within 3 months; participated in other clinical trials within 6 months.

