Depression	√	√		√		Depression will be measured by 9-item Patient Health Questionnaire (PHQ-9) [34, 35]. The score ranges from 0 to 27 and the higher score indicates higher level of depression. A score greater than 4 indicates depression.		
Anxiety	√	√		√		Anxiety will be measured by Zung’s Self Rating Anxiety Scale (SAS) [36]. The score ranges from 25 to 100 and the higher score indicates higher level of anxiety. A score greater than 49 indicates anxiety.		
Social support	√					Social support will be measured by Maternity Social Support Scale (MSSS)[37], the score ranges from 5 to 30 and the higher score indicates higher level of social support.		
Self-efficacy	√	√		√		Self-efficacy will be measured by General Self-Efficacy Scale (GSES) [38, 39]. The score ranged from 10 to 40 and the higher score indicates higher level of self-efficacy.		
The stage of gestational weight control behavior	√	√		√		The investigators will use two items to assess it. “Have the participants started to adjust their diet/physical activity to control their weight during pregnancy?“, “No and I do not plan to do so in the next 6 months/No, but I am ready to start within the next 6 months/No, but I am ready to start in the next 30 days/Yes, but not regularly/Yes, I am currently controlling my weight by adjusting my diet/physical activity regularly, but it has not reached 6 months/Yes, I have been controlling my weight for more than 6 months by adjusting my diet/physical activity” choices will be provided.		
Clinical outcomes								
Gestational Diabetes Mellitus (GDM)		√				75 g 2-hour oral glucose tolerance test (OGTT), Fasting blood, Venous blood diagnosed according to International Association of Diabetes and Pregnancy Study Group (IADPSG) criteria: Fasting plasma glucose (FPG) ≥ 5.1 mmol/L, and/or 1-h blood glucose ≥ 10.0 mmol/L, and/or 2-h blood glucose ≥ 8.5 mmol/L		
Preeclampsia/ Gestational hypertension		√		√		Preeclampsia was defined according to the criteria of the American College of Obstetricians and Gynecologists (ACOG) i.e. systolic blood pressure of ≥ 140 mmHg or diastolic blood pressure of ≥ 90 mmHg occurring after 20 weeks of gestation in a previously normotensive woman combined with new-onset proteinuria of ≥ 0.3 g/24 h. Gestational hypertension was defined similarly but without the presence of proteinuria.		

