In addition, pre-specified secondary outcomes also include changes of blood pressure, body fat percentage (%), fat free mass (kg), muscle mass (kg), attitude and knowledge, dietary intake, physical activity, sleep quality, quality of life, self-efficacy score, stage of change related to gestational weight control behavior, and incidence of depression and anxiety, which will be assessed from baseline (8^+ 0^−13^+ 6^ weeks) to midterm (24^+ 0^−27^+ 6^ weeks), and from baseline (8–14 weeks) to terminal (32^+ 0^−35^+ 6^ weeks). Incidence of postpartum weight retention, absolute/mean offspring weight, height, and head circumference will also be evaluated at 42 days, 6 months, and 12 months after delivery.

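### Depression and anxiety are specified as incidence from baseline, but women already above the cut-off can be enrolled and analysed, and the plan does not say whether new onset or prevalence is meant

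*Protocol article*

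**What the plan says.** - **Outcome.** The last paragraph of the Outcomes section ends a list of secondary outcomes with "incidence of depression and anxiety, which will be assessed from baseline" to the midterm visit and from baseline to the terminal visit. Sleep quality, quality of life and self-efficacy, in the same list, are given as changes.
- **Case definition.** Table 3 (Data collection) schedules the PHQ-9 (range 0 to 27) and the SAS (range 25 to 100) at baseline and at both follow-up visits. For the PHQ-9: "A score greater than 4 indicates depression". For the SAS: "A score greater than 49 indicates anxiety".
- **Entry.** In Eligibility and recruitment the only mental-health exclusion is "severe psychiatric disorders". No PHQ-9 or SAS limit applies.
- **Analysis.** Under Statistical analyses, the intention-to-treat analyses "include all women recruited with BMI" of 24 kg/m² or more. Linear or generalized linear mixed models, adjusted for baseline outcome values, are named for primary and secondary outcomes. The next sentence gives dichotomous outcomes a chi-squared test.

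**The concern.** Incidence counted from baseline most naturally means new onset, and new onset can occur only in women who are not cases at the start. The protocol admits baseline cases, keeps them in the analysis set, and does not say whether they leave the denominator, count as non-cases, or count as cases if they remain above the cut-off. Each choice gives a different estimate from the same data. The trial is unblinded, so the choice should be fixed before outcome data are seen.

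The chi-squared test adds a second problem. Both scales are measured before randomisation, yet the test makes no use of those measurements. Under either reading, a woman who starts above the cut-off and gets worse registers no change. A programme that asks women to record their weight weekly and tells them when gain is excessive could affect mood in either direction, so this information is worth keeping.

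**Working it through.** The protocol states no figure for depression or anxiety, so there is none to reproduce. The check sets the passages side by side and then illustrates the consequence.

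**Fit of the passages**
1. Eligibility sets no PHQ-9 or SAS limit, so women above a cut-off at baseline can be randomised.
2. The analysis set is all recruited women, so they are included.
3. If incidence is new onset, they cannot have the event, and the all-women denominator is wrong for that quantity.
4. If incidence is the proportion above the cut-off at a visit, they can be counted. The quantity is then prevalence, and a fall below the cut-off registers as recovery. A rise from an already high score does not register.
5. The chi-squared test uses baseline status under neither reading.

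Other outcomes that the protocol calls incidence largely escape this. Pre-pregnancy diabetes is excluded, and cesarean delivery and macrosomia cannot exist at baseline.

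**Illustration**

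From the protocol: 200 women at 1:1, 10% attrition, two-sided α = 0.05. Evaluable women per arm = 100 × (1 − 0.10) = 90.

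Assumed: baseline prevalence b from 0 to 50%; new onset 20% (control) and 10% (intervention) among women not above the cut-off at baseline; 60% of baseline cases remain cases in both arms.

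- A, new onset in women at risk: n = 90(1 − b) per arm, 20% vs 10%.
- B, all women, baseline cases counted as non-cases: 0.20(1 − b) vs 0.10(1 − b).
- C, proportion above the cut-off at the visit: 0.60b + 0.20(1 − b) vs 0.60b + 0.10(1 − b).

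Power = Φ{[|p₁ − p₂| − 1.96·√(2p̄(1 − p̄)/n)] / √([p₁(1 − p₁) + p₂(1 − p₂)]/n)}, where p̄ is the mean of the two proportions.

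At b = 0.30:
- A: n = 90 × 0.70 = 63.
- B: 0.20 × 0.70 = 14% vs 0.10 × 0.70 = 7%.
- C: 0.18 + 0.14 = 32% vs 0.18 + 0.07 = 25%.

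| b | A: n per arm; rates; power | B: rates; power | C: rates; power |
|---|---|---|---|
| 0% | 90; 20 vs 10%; 0.467 | 20 vs 10%; 0.467 | 20 vs 10%; 0.467 |
| 10% | 81; 20 vs 10%; 0.429 | 18 vs 9%; 0.423 | 24 vs 15%; 0.330 |
| 30% | 63; 20 vs 10%; 0.348 | 14 vs 7%; 0.333 | 32 vs 25%; 0.178 |
| 50% | 45; 20 vs 10%; 0.262 | 10 vs 5%; 0.245 | 40 vs 35%; 0.102 |

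The three agree only when nobody is above the cut-off at baseline. C fares worst here because persistence was assumed equal in both arms. If the intervention also helped recovery, C would gain, so the ordering is not general.

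**Score against cut-off**

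For a normally distributed score, splitting it so that a proportion p lies above the cut-off keeps φ(z)²/[p(1 − p)] of the information, where z is the matching normal quantile. This gives 0.49 at p = 0.20, 0.60 at 0.35 and 0.63 at 0.45. Here p is the proportion at follow-up, also assumed. A baseline covariate with assumed correlation 0.5 leaves 1 − 0.5² = 0.75 of the residual variance.

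**The case against.** The best defence is that the protocol uses the word incidence loosely. It writes of the incidence of cesarean delivery, macrosomia and postpartum weight retention, meaning the proportion of women with the condition. The phrase about assessment from baseline closes a long list that opens with changes, and Table 3 applies one fixed cut-off at every visit without reference to earlier status. Visit prevalence is therefore a plausible intention. This stands, but the text does not settle it, and the wording would then need correcting.

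Two stronger inferences should be resisted:
- A reader might infer that women above a cut-off at baseline can never contribute. Under visit prevalence they do, since recovery turns them into non-cases.
- A reader might infer that leaving them out destroys the randomised comparison. The Randomization section requires the baseline assessment to be complete before allocation, so restriction on that measurement is valid. It answers a narrower question than the all-women analysis in the protocol.

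It can also be said that a generalized linear mixed model adjusted for baseline values would use baseline status, and that an analysis plan not shown could fix the denominator. The first is partly right, but the protocol goes on to assign dichotomous outcomes to the chi-squared test, and adjustment does not define a case or an at-risk set. On the second, the protocol has itself fixed the outcome type, the cut-offs, the population and the test. A later plan would have to reinterpret or depart from one of them.

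**Conclusion.** The point holds as an ambiguity in the outcome combined with a weak choice of analysis. Either incidence is new onset and does not fit the all-women denominator, or it is prevalence under the wrong name. In both cases the chi-squared test discards the baseline measurement.

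The size cannot be fixed from the protocol, which gives no baseline prevalence for either scale. The illustrated differences of 10 points under A and 7 points under B and C, at 30% prevalence, rest wholly on the assumed prevalence, onset and persistence. The efficiency figures rest on a normal score and an assumed split. A reader might take a particular share of the 200 women to be lost to these outcomes, but nothing in the protocol supports any such number.

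Only secondary outcomes are affected. The gestational weight gain outcomes and the sample size are not. The change is still worth making because the data are already scheduled and the cost is small.

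**What to change.** 1. Make the PHQ-9 and SAS scores at 24 to 27 and 32 to 35 completed weeks the outcomes, with the baseline score as covariate, in the models already named under Statistical analyses. Every woman with a follow-up score then counts, and both improvement and worsening register.
2. As support, report the proportion above each cut-off at each visit in all women, call it prevalence, and compare arms with a model adjusted for baseline status in place of the chi-squared test.
3. If new onset is also of interest, define it in women at or below the cut-off at baseline and state that this is a narrower population.

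The cost is a change of outcome wording and analysis text. No visit, questionnaire or participant is added. The downside is that a difference in mean score is less direct to interpret than a proportion, which is why the proportion stays as support.

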#### Measures about mother and infant 

women’s weight, blood pressure before delivery, infants’ gestational age at birth, birth weight, recumbent length at birth, Apgar scores, et al. will be obtained from EMR at one week after delivery. Maternal postpartum weight, and infants’ height, weight, head circumference at 42 days, 6 months and 1 year after delivery will be obtained through routine physical examination or telephone follow-up.

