## Discussion

Excessive gestational weight gain (EGWG) has been shown to amplify the effect of overweight or obesity on the risk of GDM, macrosomia, large for gestational age(LGA), and adverse health outcomes during childhood and adolescence, such as obesity, early puberty, and type 2 diabetes [7]. Preventing EGWG among high-risk pregnant women may have the greatest long-term effects in promoting the health of both mothers and offspring. Although a large amount of EGWG intervention study has been carried out, there was considerable heterogeneity among different intervention studies, including type, intensity of the intervention provided, the amount and type of face-to-face contact provided within the intervention, and whether it was performed based on mobile health or not, etc [40]. There is an urgent need for a widely recognized mobile health-based intervention models for the effective prevention of EGWG, especially for high-risk pregnant women such as overweight or obesity before pregnancy.

The HGWG-pro trial is designed to advance our knowledge of mobile health-based lifestyle interventions to optimize GWG and other health outcomes in pregnant women who are overweight or obese, as well as in their offspring. Strengths of the trial design include recruitment from two regions with different economic levels, the guidance of the transtheoretical model, the support with mobile health technologies (APP and wristband), focusing on changing 8 unhealthy dietary behaviors. Data collection strengths include rigorous assessment of food frequency, assessment of participants’ objective physical activity during pregnancy by collecting data through Wechat APP and wristband, collection of participants’ blood and urine samples at three different stages of pregnancy, as well as cord blood, to evaluate the cardiometabolic profile and creation of a biorepository for future study. The 12-month follow-up data will facilitate determining whether potential improvements in GWG are associated with improvements in postpartum weight retention and child growth and development indicators. It can serve as the first examples of a rigorously designed and evaluated EGWG prevention program improving dietary and exercise behaviors in China.

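### Postpartum weight retention is named only as an incidence, without a cut-off or reference weight, although the weights needed to analyse it in kg are already collected

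*Protocol article*

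**What the plan says.** The relevant text in the protocol article is as follows.

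- Outcomes: "Incidence of postpartum weight retention" is listed for the visits at 42 days, 6 months and 12 months. In this one sentence maternal retention is an incidence, while the offspring measures are kept on their natural scale. No cut-off or reference weight for retention appears anywhere in the article.
- Measures about mother and infant: "Maternal postpartum weight, and infants’ height, weight, head circumference at 42 days, 6 months and 1 year after delivery will be obtained", and these data "will be obtained through routine physical examination or telephone follow-up".
- Table 3 and the Data collection text: pre-pregnancy weight is self-reported and taken from the medical record, with an early-pregnancy weight as fallback.
- Outcomes, primary: gestational weight gain (GWG) is the weight at the visit minus pre-pregnancy weight, kept in kg.
- Statistical analyses: linear regression or generalized linear mixed models cover primary and secondary outcomes, including those at 42 days, 6 months and 12 months, with adjustment for clustering and baseline values. Chi-squared tests cover the proportion above the IOM rate "and other dichotomous outcomes".
- Discussion: the 12-month data are meant to show "whether potential improvements in GWG are associated with improvements in postpartum weight retention".

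**The concern.** Retention is the same subtraction as the primary outcome, made later: a weight minus the pre-pregnancy weight. The plan keeps the kg scale during pregnancy but, for the mother after delivery, names only a yes/no version. Dichotomising a continuous measurement loses information at any cut-off, and writing in a cut-off does not bring it back. So the point is not only a missing definition: the scale named is the weaker of two available scales.

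The abstract presents follow-up to 12 months as a distinctive feature of the trial, and retention is the maternal weight outcome named for that period. What is at stake is the precision of that comparison, and of the link between GWG and retention that the Discussion wants to draw.

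The absence of a cut-off also stands out because other binary outcomes in the article carry theirs: "incidence of macrosomia (with infant birth weight ≥ 4000 g"; the glucose limits for gestational diabetes; the blood pressure limits; and, for the PHQ-9, "A score greater than 4 indicates depression".

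**Working it through.** The plan states no power or precision for retention, so there is no figure of its own to reproduce. The sample size section concerns GWG only.

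**Step 1. Information kept after dichotomising.** Assume retention is about normal (not stated in the documents). Let p be the proportion classed as retained, z the standard normal point with p above it, and φ the normal density. A small shift in the mean, in SD units, moves the proportion by φ(z) times that shift, and the variance of the yes/no value is p(1 − p). The information kept, relative to the kg analysis, is therefore

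E = φ(z)² / [p(1 − p)].

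The incidences below are assumptions, since the documents give none.

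- p = 0.5: z = 0, φ = 0.3989, E = 0.1592 / 0.25 = 0.637
- p = 0.3: z = 0.524, φ = 0.3477, E = 0.1209 / 0.21 = 0.576
- p = 0.2: z = 0.842, φ = 0.2800, E = 0.0784 / 0.16 = 0.490

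The maximum is at p = 0.5, so at least 36% is lost at any cut-off. The sample size does not enter the formula.

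**Step 2. What that means for power.** Take any difference that the kg analysis would detect with 80% power at two-sided 5%. Its standardised size is 1.960 + 0.842 = 2.802. After dichotomising, power is about Φ(2.802 × √E − 1.960).

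- E = 0.637: Φ(2.236 − 1.960) = Φ(0.276) = 0.61
- E = 0.576: Φ(2.127 − 1.960) = Φ(0.167) = 0.57
- E = 0.490: Φ(1.961 − 1.960) = 0.50

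To get back to 80%, the binary comparison needs 1/E times as many women: 1.57, 1.74 and 2.04 times.

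**Step 3. Direct check.** Assume 90 women per arm (100 less the 10% attrition in the sample size section, which is not stated for the postpartum visits), control mean 3 kg and SD 5 kg. The difference giving 80% power in kg is 2.802 × 5 × √(2/90) = 2.09 kg.

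- Cut-off 2 kg: 57.9% against 41.4%, power 60%.
- Cut-off 5 kg: 34.5% against 20.7%, power 54%.

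Over assumed SDs of 4 to 6 kg and control means of 1 to 3 kg, with the kg analysis held at 80%, power at a 5 kg cut-off is 39% to 56%. Over the cut-offs tried (0 to 7 kg), the binary comparison needs at least 143 per arm for 80% power, and 143/90 = 1.59 agrees with Step 2.

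**Step 4. Which analysis the incidence would get.** The Statistical analyses section supports two readings. A binary retention outcome is a dichotomous outcome, which points to chi-squared. It is also a secondary outcome at the three postpartum visits, which points to the adjusted models, and a generalized linear mixed model can take a binary response. The text does not settle it. The loss in Step 1 comes from the scale and arises on either route.

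**The case against.** Four objections deserve weight.

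- **The data themselves are not reduced.** Weight is collected, and the planned linear and mixed models could analyse it in kg. That is true, and it is why the change is cheap. But no retention outcome in kg is listed for those models to analyse.
- **The missing cut-off may be condensation.** This is a journal article, and the full protocol and analysis plan are not shown. A reader might infer that the threshold will be picked after the data are seen. The documents do not support that, because either unseen document may fix it. In a simulation with 90 per arm, mean 3 kg and SD 5 kg (all assumed), taking the best of cut-offs 0, 2 and 5 kg raised the error rate at one visit from 5% to about 11.8%. That shows why the cut-off should be fixed, not that it will be chosen late.
- **The comparison need not be unadjusted.** A reader might infer a plain chi-squared test. As Step 4 shows, an adjusted model is equally open on the text.
- **A proportion answers a legitimate question of its own.** This stands, and it is a reason to keep the incidence beside the mean.

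Two smaller points also stand. The Discussion sentence on GWG and retention does not itself fix a binary scale. Weights reported by telephone would add error to either version, and the change of scale does not cure that.

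**Conclusion.** The point holds for the scale of one secondary outcome. Maternal retention is named only as an incidence, without a definition, when a more informative outcome can be computed from weights already collected. Under approximate normality the yes/no version keeps at most about 64% of the information, 58% at an assumed 30% incidence and 49% at an assumed 20%.

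These percentages rest on normality and the assumed incidences, not on how many women are followed after delivery. It is tempting to turn them into a number of women lost, using the 180 left after the stated 10% attrition. That rate comes from the calculation for GWG in pregnancy, and the documents give no postpartum figure, so such head-counts are not supported. The power values in Step 3 are illustrations on assumed SDs, means and cut-offs.

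The two primary outcomes are continuous in kg, and the conclusions drawn from them are unaffected.

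**What to change.** In Outcomes, name mean postpartum weight retention in kg, defined as postpartum weight minus pre-pregnancy weight, at 42 days, 6 months and 12 months. In Statistical analyses, assign it to the linear or mixed model already planned, adjusted for pre-pregnancy BMI and hospital.

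Keep the incidence as a supplementary outcome. State its cut-off and reference weight before the data are seen, and say which of the two analysis routes applies to it. If the full protocol or analysis plan already defines it, carry that definition into the outcome list.

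The cost is the wording of one outcome and one analysis sentence. No new measurement, visit or participant is needed.
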